### Outcomes

2.5.

The primary outcome of the intervention will be measured by its effects (1) on quality of life and (2) memory function.

Changes in quality of life among PWE enrolled in the study will be estimated by comparing scores of the Quality of Life in Epilepsy 31-item inventory (patient weighted version, QOLIE-31-P) that has been validated in Lithuania and is among the most frequently used standardized quality of life assessment tools in PWE (9, 10). By selecting quality of life as the primary endpoint, we intend to detect broader effects of the intervention (i.e., beyond objective cognitive performance) representing direct benefits to participating PWE.

Verbal memory will be assessed by using the Lithuanian equivalent of the Rey Auditory Verbal Learning Test (RAVLT) that consists of five learning trials of a 15-word list A, one learning trial of a word list B and measuring the delayed recall of the word list after 30 min (11). Visual recall at 30 min will be measured by using the Medical College of Georgia (MCG) Complex Figure test for repeated testing (12).

Secondary outcomes will include symptoms of depression (Neurological Disorders Depression Inventory in Epilepsy, NDDI-E) (13, 14), anxiety (General Anxiety Disorder-7, GAD-7) (15) and suicidality (Columbia Suicide Severity Rating Scale, C-SSRS) (16), metacognition (Metacognition Questionnaire-30, MCQ-30) (17, 18), Jacoby’s 3-item Stigma Scale (19), antiseizure drug adverse effects (Liverpool Adverse Events Profile, LAEP) (20, 21), health-related quality of life [the Short Form (36) Health Survey] (22) and subjective evaluation of cognitive functions (*ad hoc* Likert scales 0 to 10). Secondary cognitive outcomes will include reaction speed (Trail Making Tests A and B, Maze Task), working memory (Digit Span Test), verbal fluency (categorical and phonemic naming in 60 s), autobiographical memory (naming of recent personal autobiographical events), delayed verbal story recall as well as 1-week verbal recall to test for accelerated long-term forgetting. An experimental task set to test learning and recall of a hypothetical weekly schedule will also be used (Figure 1). This task was created by the authors and will be explored for applicability in testing for real-world event data, such as memory of where (e.g., in conference room 62B of the office), when (e.g., Monday at 15:30) and for what purpose (e.g., to be present in a business meeting) the participant is hypothetically planning to participate. The task will also include an item about preparatory actions before each activity (e.g., familiarize with material of the meeting in the latter example) and will be scored for each item recalled (maximum of 20 points). Given the exploratory nature of the task, it has not been previously validated and will rely on comparison between early and late intervention groups.

**Figure 1 fig1:**
[figure not shown]
An example of a figure used in the experimental memory task. The figure will serve as a learning aid to memorize items of one week’s schedule, including place, time, and activity, as they are being read by the investigator. Participants will be asked to recall the same data after 30 min.

The possible learning effects at post-interventional follow-ups will be mitigated by using three different versions of the same memory tests as well as by comparing memory function in late vs. early intervention groups rather than improved performance in comparison to baseline scores in each subgroup.

BOX 1Outline of the content of the CoRE intervention.CoRE intervention plan (8 weeks)1. Individual session.■ Familiarization.■ Goal setting. Discussion of the plan.■ Presentation of the Mind-Emotion-Body connection.■ Homework.2. Individual session.■ Discussion of homework.■ Thought exercises.■ Thinking training. Visual memory.■ Homework.3. Individual session.■ Discussion of homework.■ Body senses. Attention training.■ Physiology training.■ Homework.4. Individual session.■ Discussion of homework.■ Working with emotions. Influence of emotions on quality of life and memory.■ Emotion regulation.■ Memory training.■ Homework.5. Individual session.■ Discussion of homework.■ Attention management.■ Metacognition training.■ Self-regulation.■ Homework.6. Individual session.■ Discussion of homework.■ Positive psychology.■ Strengths and resources.■ Memory training.■ Homework.7. Group session.■ Discussion of homework.■ The importance of social support.■ Creating a circle of support.■ Attention training.■ Homework.8. Group session.■ Discussion of homework.■ Compassion for self and others.■ Memory and quality of life.■ Homework. Summing up.General plan of a 60-min session:■ 10 min: presentation of the topic and discussion of homework.■ 20 min: teaching of the topic.■ 20 min: skill building.■ 10 min: reflection. Questions. Homework.

Demographic (sex, age, educational and professional status, personal relationship status, socioeconomic status) and clinical (seizure type, epilepsy type, epilepsy etiology, epilepsy duration, seizure frequency, antiseizure medications used, seizure and electroencephalography laterality, localization of seizure focus (if present), handedness, somatic comorbidities) data of each participant will be collected to predefined case report forms.

### Participant recruitment, allocation, and timeline

2.6.

Study participants will be invited to participate in the trial during routine outpatient visits at the epilepsy clinic. They will have either temporal lobe or genetic generalized epilepsy as confirmed by the epileptologist, according to previously collected clinical (e.g., seizure semiology, patient history), instrumental (e.g., electroencephalography, video-electroencephalography), genetic and imaging (e.g., 3T magnetic resonance imaging) data required to substantiate the diagnosis according to guidelines by the International League Against Epilepsy. After acceptance, each new participant will be randomly assigned to either the early intervention group (EIG) or the late intervention group (LIG) at the time of enrolment by using open-source software for minimization (WinPepi) based on sex, epilepsy type and seizure control. The randomization will be done, and participants assigned to one of the groups by the principal investigator. Outcome assessors and data analysts will be blinded to participant status by using concealed patient coding and instructing patients not to discuss their status during examination. The principal investigator, psychologists performing the intervention and participants themselves will not be blinded.

Both the EIG and the LIG will undergo neuropsychological assessment at three time points (Figure 2). The EIG will be tested at baseline, with two follow-ups four and sixteen weeks after the intervention which itself lasts for eight weeks. The LIG will be tested at the same time points while on waitlist. Participants assigned to the LIG will be offered the intervention after the second follow-up. Both groups will receive otherwise routine clinical care (i.e., according to individual needs and best medical practice) at the tertiary epilepsy clinic. Given the non-invasive nature of the CoRE intervention, no adverse effects are expected. Therefore, discontinuation of the intervention is expected to occur only in the case of participant dropout. Patient attrition will be minimized by thoroughly discussing the aims and procedures of the trial before enrolment as well as by accommodating to the patients’ availability and daily schedule for the weekly sessions.

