### Eligibility criteria

2.3.

Patient enrolment and clinical evaluation will be done by a certified neurologist and include the following inclusion and exclusion criteria:

Inclusion criteria:

Active epilepsy (medication for epilepsy and/or had at least one seizure in the past year).Adults (≥18 years).Lithuanian speakers.No intellectual disability.

Exclusion criteria:

Sensory or motor deficit preventing task completion.Epilepsy surgery planned during the project.Active non-paroxysmal comorbid disorder of the central nervous system (e.g., neurodegeneration, multiple sclerosis).Active psychiatric disorder during the past year.Psychoactive substance use (except social alcohol, tobacco and caffeine use).

Patients with temporal lobe epilepsy as well as genetic generalized epilepsy will be enrolled.

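### As written, assignment by the unblinded principal investigator comes before baseline testing, so baseline self-reports may be given with knowledge of group and the next assignment is not concealed from its operator

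*Protocol article*

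**What the plan says.** Section 2.6 of the protocol article (Participant recruitment, allocation, and timeline) states that, once a patient has accepted, "each new participant will be randomly assigned to either the early intervention group (EIG) or the late intervention group (LIG) at the time of enrolment", and that this is done "by using open-source software for minimization (WinPepi) based on sex, epilepsy type and seizure control". On who does it: "The randomization will be done, and participants assigned to one of the groups by the principal investigator". On who knows the result: "The principal investigator, psychologists performing the intervention and participants themselves will not be blinded". Outcome assessors and data analysts are to be kept blind "by using concealed patient coding and instructing patients not to discuss their status during examination".

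The next paragraph of section 2.6 turns to assessments of the groups so formed: "The EIG will be tested at baseline, with two follow-ups four and sixteen weeks after the intervention". The late group is tested at the same times while waiting and is offered the programme after the second follow-up.

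Two other places bear on the order of steps and the roles. The Ethics statement puts written consent at enrolment. Section 2.3 (Eligibility criteria) says "Patient enrolment and clinical evaluation will be done by a certified neurologist", without saying whether that neurologist is the principal investigator.

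**The concern.** There are two exposures.

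**Baseline.** QOLIE-31-P, one of the primary measures, is filled in by the participant. So are secondary scales such as NDDI-E and GAD-7. A blinded assessor cannot protect an answer given by a respondent who knows the group. Someone just told to wait through the 8-week programme and 16 further weeks (8 + 16 = 24 weeks) may answer differently from someone about to start. Baseline is one of the three time points in the planned repeated-measures ANOVA, and ANCOVA is named for secondary analyses. A reaction to allocation would then enter the analysis as if it were a pre-treatment value, and no later analysis can recover the uncontaminated baseline.

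**Concealment.** The measures described (patient coding, and asking patients not to talk about their status) protect assessors and analysts. None of them hides the upcoming assignment from the person who operates the minimisation, and that person is unblinded. If the same person also influences who enters and when, selection becomes possible.

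**Working it through.** **Order of steps.** No single sentence gives the order, so it has to be assembled:

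1. Consent is given at enrolment (Ethics statement), so consented baseline testing cannot come before enrolment.
2. Assignment happens at enrolment (section 2.6).
3. Baseline is described as the first test of participants already labelled early or late (section 2.6).
4. The instruction not to discuss status during examination makes no exception for the baseline visit (section 2.6).

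The plain reading is assignment first, baseline second. Figure 2 is not shown, and the moment at which participants learn their group is not given.

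**The plan's own sample size.** Inputs from section 2.7: f = 0.40, α = 0.05, 0.95 (printed as β, read as power), two groups, m = 3 measurements, ρ = 0.5. For the between-group main effect:

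λ = f²·N·m / (1 + (m − 1)ρ) = 0.16 × 58 × 3 / 2 = 13.92, with 1 and 56 df, giving power 0.956.

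This reproduces N = 58, and 58 × 1.2 = 69.6, hence 70. Interaction versions of the calculation give 18, 50 or 52, not 58. Section 2.7 nevertheless calls the target a between-group interaction, so both tests are examined below.

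**Effect of a baseline shift (assumption).** Suppose that knowing the group shifts baseline self-report by b SD between arms, that the shift has gone by both follow-ups, and that there is no treatment effect. The group differences over time are (b, 0, 0). With n = 29 per arm, ρ = 0.5 and compound symmetry:

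- Group-by-time: λ = (n/2)(2b²/3)/(1 − ρ) = 14.5 × 0.6667b² / 0.5 = 19.33b², with 2 and 112 df.
- Main effect: λ = (n/2)·3·(b/3)²/(1 + 2ρ) = 14.5 × 0.3333b² / 2 = 2.417b², with 1 and 56 df.

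| Assumed b (SD) | λ, group-by-time | Type I error | λ, main effect | Type I error |
|---|---|---|---|---|
| 0.1 | 0.193 | 6.4% | 0.024 | 5.3% |
| 0.2 | 0.773 | 11.1% | 0.097 | 6.1% |
| 0.3 | 1.740 | 19.7% | 0.218 | 7.4% |

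With 35 per arm the group-by-time figures are 6.8%, 12.5% and 23.1%.

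**If the shift lasts.** The late group still knows its status and is still waiting at both follow-ups, so a lasting shift is also plausible. For b = 0.2:

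- Change score: bias is 0.2 in size if transient, and 0.2 − 0.2 = 0 if persistent.
- ANCOVA with slope 0.5: bias is 0.5 × 0.2 = 0.1 in size if transient, and 0.2 − 0.5 × 0.2 = 0.1 if persistent.

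For scale at N = 58, the standard errors are sqrt(4/58) = 0.263 SD for a change score and sqrt(0.75 × 4/58) = 0.227 SD for ANCOVA. The planned effect f = 0.40 in two groups corresponds to 2 × 0.40 = 0.8 SD.

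**Predictability of assignment.** The article gives no probability for the favoured arm. A simulation of 1,000 trials of 70 participants, with minimisation on three evenly split binary factors (assumption), shows how often someone who knows the past assignments guesses the next one correctly:

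| Probability of favoured arm | Correct guesses |
|---|---|
| 0.5 | 50% |
| 0.7 | 68% |
| 0.8 | 75% |
| 0.9 | 83% |
| 1.0 (deterministic) | 89% |

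**The case against.** The strongest reply is that the order is inferred. Describing baseline by arm is ordinary shorthand for each arm's schedule. The timeline figure is not visible, and an article may leave the timing of disclosure to the full protocol. It stands that the article does not say outright that baseline follows disclosure, and a reader should not report that as a stated fact. But the text fixes assignment at enrolment and names who performs it. Someone following it literally would assign first.

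Second, a reader might infer that assignment is largely predictable and that selection occurs. The documents do not support that. The random element is not stated, patients accept before they are assigned, and the enrolling neurologist is not identified as the principal investigator. What stands is that no separation between recruiting and assigning is described.

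Third, a reader might take the raised type I error as a route to a false claim of benefit. If the late group is disappointed at baseline and the effect fades, that group appears to gain more, so the bias runs against the intervention. If the effect lasts, the change score is unbiased. With a baseline taken before assignment, a lasting 0.2 SD shift would appear in full in both the change score and ANCOVA. That is an expectation effect of any unblinded waitlist comparison, and reordering the steps does not remove it. All of this stands, and it is why no direction is claimed.

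Fourth, delayed verbal and visual recall are tested by blinded assessors, and section 2.5 says that memory will be judged between groups rather than against each group's baseline. Nothing in the article shows that knowing the group alters effort on these tests. The exposure therefore lies mainly with the self-reports.

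**Conclusion.** The point holds as a design risk that should be removed before recruitment, not as a demonstrated bias. Followed as written, section 2.6 leaves baseline QOLIE-31-P and the secondary self-report scales open to knowledge of allocation, and it leaves the next assignment unconcealed from an unblinded operator.

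The size is unknown. Under an assumed transient shift of 0.1 to 0.3 SD with 29 per arm, type I error would be about 6% to 20% for the group-by-time test and about 5% to 7% for the between-group main effect. The second test is the one that the stated 58 matches, so the smaller figures may be the relevant ones. If the shift persists to follow-up, the change-score bias disappears.

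Predictability ranges from no better than chance to 89%, depending on a random element that the article does not give.

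**What to change.** State in section 2.6, and follow, this order: consent, eligibility, full baseline assessment, then minimisation and disclosure of the group. If that is already the intention, one corrected sentence is enough.

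Have an existing team member who neither recruits nor assesses run the minimisation on receipt of a completed enrolment form, and state the random element used in each assignment. Probability 0.8 for the favoured arm is one example. It still allows about 75% correct guesses by someone who holds the running tally, so separating the roles does most of the work.

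The cost is two existing steps reordered and one task moved within the team. The sample size and the number of visits do not change. Balance on the three factors becomes marginally looser, and participants learn their group slightly later. If baseline includes the one-week recall listed in section 2.5, that delay is about a week. Table 1 shows that recruitment had not started and ethics approval was pending when the article was written, so the change could be made before the first participant.

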### Sample size and statistical analysis

2.7.

The target sample size of the study was calculated for a between-group interaction of a two-way repeated measures analysis of variance (ANOVA) with *f* = 0.40, *α* = 0.05, *β* = 0.95, two groups (early and late intervention), three measurement points, and 0.5 correlation between repeated measures. The resulting sample size of *n* = 58 (G*Power 3.1.9.7) was increased by 20% to *n* = 70 to account for dropouts (including the possibility of patient referral to presurgical evaluation if needed according to principles of best medical practice) and corresponded well to the mean sample size and attrition rates in previous trials (5). This sample size is deemed achievable as the trial will be conducted in a large university hospital covering tertiary epilepsy care services for approximately 1.4 million of inhabitants and include a group of PWE composed of patients with both TLE and GGE.

The efficacy of the intervention will be defined as statistically significant improvement on one of the primary outcomes (quality of life or delayed memory), tested with a repeated-measures between-factors analysis of variance (ANOVA) in the EIG as compared to the LIG. For secondary analyses, dynamic changes of other outcome measures will be tested, respectively, by using ANOVA or ANCOVA. The association between demographic and clinical variables with study endpoints will be conducted by means of linear and ordinal regression modeling. Subgroup analyses are planned to be conducted based on sex, education status, professional status, epilepsy type, laterality and lesionality. In case of missing data, multiple imputation will be used in sensitivity analysis.

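### The primary ANOVA leaves out the three minimisation factors, so the between-group test is conservative and loses some power if those factors are prognostic

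*Protocol article*

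**What the plan says.** Section 2.6 (Participant recruitment, allocation, and timeline) assigns each new participant to the early (EIG) or late (LIG) intervention group "by using open-source software for minimization (WinPepi) based on sex, epilepsy type and seizure control".

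Section 2.7 (Sample size and statistical analysis) defines efficacy as a significant improvement on a primary outcome, "tested with a repeated-measures between-factors analysis of variance (ANOVA) in the EIG as compared to the LIG". No minimisation factor is named in that test. Covariate adjustment appears in the next sentence, for other outcomes: "For secondary analyses, dynamic changes of other outcome measures will be tested, respectively, by using ANOVA or ANCOVA". Demographic and clinical variables are handled in separate regressions and in subgroups: "Subgroup analyses are planned to be conducted based on sex, education status, professional status, epilepsy type, laterality and lesionality". Sex and epilepsy type are on that list; seizure control is not.

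The same section says that the sample size was "calculated for a between-group interaction of a two-way repeated measures analysis of variance (ANOVA"), with f = 0.40, α = 0.05, two groups, and "three measurement points, and 0.5 correlation between repeated measures". It prints β = 0.95, which can only be meant as power. So the powered effect is called an interaction, while the efficacy test is called a between-factors ANOVA.

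Two other places mention adjustment. The Discussion plans to adjust for subclinical anxiety and depression. The Limitations section says that heterogeneity in epilepsy type will be met by subgroup and adjusted analyses. Neither is tied to the primary test.

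**The concern.** Minimisation makes the two groups more alike on its factors than simple randomisation would. If the factors predict the outcome, the true sampling variation of the group difference shrinks. An ANOVA without the factors does not register this: the variance they explain stays in its error term, so the reported standard error exceeds the real one. Confidence intervals are then too wide, the real type I error falls below 5%, and power is given away.

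In a trial of 70 patients mixing temporal lobe and genetic generalized epilepsy, the stake is a higher chance of missing a real effect, at a price that is easily avoided. How much is lost depends on how prognostic the factors are and on whether the tested effect is the group effect or the group-by-time interaction.

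**Working it through.** **Inputs from section 2.7.** f = 0.40, α = 0.05, power 0.95, k = 2 groups, m = 3 measurements, ρ = 0.5, n = 58 before dropout. From section 2.6: three minimisation factors.

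**Assumptions.** R², the share of the variance of a patient's mean score explained by the three factors, is not in the protocol. I use 0.05 to 0.30. Each factor is taken to have two levels.

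**Step 1. Reproduce n = 58 (noncentral F).**
- Between-group effect: λ = f²·N·m / (1 + (m − 1)ρ), with 1 and N − 2 df. At N = 58, λ = 0.16 × 58 × 3 / 2 = 13.92 and power is 0.956. At N = 56, λ = 13.44 and power is 0.9495, just short. So 58 reproduces.
- Group-by-time interaction: λ = f²·N·m / (1 − ρ), with 2 and 2(N − 2) df. N = 18 already suffices (λ = 17.28, power 0.953). So 58 does not reproduce.

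The figures therefore belong to the between-group effect, whatever the word interaction was meant to convey.

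**Step 2. Add the three factors to the between-group test.** λ becomes 13.92 / (1 − R²), and error df falls from 56 to 53. The unadjusted standard error is larger than the adjusted one by the factor 1/√(1 − R²).

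| Assumed R² | λ | Unadjusted SE larger by | Adjusted power, n = 58 | N for 95% power |
|---|---|---|---|---|
| 0 | 13.92 | 0% | 0.956 | 58 |
| 0.05 | 14.65 | 2.6% | 0.964 | 54 |
| 0.10 | 15.47 | 5.4% | 0.971 | 52 |
| 0.20 | 17.40 | 11.8% | 0.984 | 46 |
| 0.30 | 19.89 | 19.5% | 0.992 | 42 |

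At R² = 0 the three lost degrees of freedom leave power at 0.956.

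**Step 3. Type I error.** With perfect balance, the real size of the unadjusted test is 2·P(Z > 1.96/√(1 − R²)): 3.9%, 2.8% and 1.9% for R² = 0.10, 0.20 and 0.30. Minimisation does not balance perfectly, so I rely on simulation. The settings are biased-coin minimisation with an assumed 0.8 probability of the balancing arm, three balanced binary factors, N = 58 and 3,000 runs per scenario. The Monte Carlo standard error near 5% is √(0.05 × 0.95 / 3000) = 0.4 percentage points.

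Between-group test, factor effects stable over time:
- R² = 0.10: unadjusted type I error 4.1%; power 0.44 unadjusted and 0.49 adjusted.
- R² = 0.30: mean model SE 0.214 against a true SD of 0.186; type I error 2.5%; power 0.44 unadjusted and 0.59 adjusted.

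The power figures use an effect of 0.6 SD at both follow-ups and none at baseline. Averaged over three time points this is 0.6 × 2/3 = 0.4 SD, or f = 0.20, half the design effect. They show what happens if the true effect is smaller than planned.

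**Step 4. Group-by-time contrast** (mean of the two follow-ups minus baseline), R² = 0.30:
- Stable factor effects: SE 0.227 unadjusted and 0.228 adjusted; type I error 5.2% for both; power 0.735 and 0.733. The factors cancel within the patient and nothing is lost.
- Factors also affecting change (their effect doubled at follow-up): unadjusted type I error 3.6%; power 0.64 unadjusted and 0.73 adjusted.

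**Step 5. Baseline as covariate** (mean of the two follow-ups as outcome, same 0.6 SD effect, stable factor effects): power without and with the three factors is 0.884 and 0.888 at R² = 0.10, and 0.895 and 0.917 at R² = 0.30. Baseline already carries much of what the factors explain. If the factors also affect change, the gain stays large (0.69 to 0.91 at R² = 0.30).

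**The case against.** The strongest objection is that this is a condensed article. The covariate list of a primary model is often left to the statistical analysis plan, which is not shown, and the article nowhere says that the ANOVA is unadjusted. Its two mentions of adjustment point towards covariates. What stands is that one cannot say the final analysis will omit the factors. But the article does more than stay silent: it names the primary model, places ANCOVA under secondary analyses, and leaves its mentions of adjustment unattached to the efficacy test. A plan that followed section 2.7 would inherit a model without the factors.

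Second, section 2.7 also speaks of an interaction, and for that test stable factor effects cancel. This stands and makes the point conditional. Against it, only the between-group effect yields 58, and the Outcomes section says that memory will be compared between the late and early groups rather than with each group's baseline.

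Third, the size rests on an assumed R², and no reason is given for choosing these three factors. A reader might infer that they were picked as known predictors of quality of life and memory; the protocol does not say so. Fourth, at the design effect the gain is only about 1 to 1.5 power points for R² of 0.05 to 0.10. Both points stand.

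**Conclusion.** The point holds in a limited form. The named primary test does not include the factors used to allocate. For the between-group effect that test is conservative if the factors are prognostic: about 4.1% to 2.5% real type I error for an assumed R² of 0.10 to 0.30. Adjustment would lift power at f = 0.40 and n = 58 from 0.956 to about 0.97 to 0.99. The loss is larger if the true effect is smaller than planned. R² is an assumption throughout and may differ between the three primary outcomes.

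A reader might infer more than this, and the protocol does not support it:
- That standard errors are too large whichever effect is tested. For the group-by-time interaction this is so only if the factors affect change over time.
- That the trial is underpowered for lack of adjustment. On its own inputs the unadjusted between-group test has 0.956 power at n = 58.
- That a positive finding would be unsafe. The error is in the conservative direction, so a significant result stays valid.

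The change is worth making because it costs almost nothing even if the factors turn out not to be prognostic.

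**What to change.** In section 2.7, add that the primary model includes sex, epilepsy type (TLE/GGE) and seizure control as fixed covariates, coded as in the minimisation. State also whether the tested effect is the group effect or the group-by-time interaction. If it is the interaction, the sample-size statement needs to be brought into line, since n = 58 does not come from that test.

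The cost is two sentences and, with two-level coding, three degrees of freedom. No new data are needed: sex and epilepsy type are among the case report form items listed in the Outcomes section, and seizure control must be known to run the minimisation. The change should be fixed before unblinding.

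Adjusting for the baseline score is a separate and larger decision. Baseline is one of the three repeated measurements, so as a covariate it must be removed from the repeated outcomes. That alters the model and the three-measurement basis of the sample size, and the further gain from the three factors would then probably be smaller.
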